## Discussion

Our work will describe the molecular mechanisms of circadian rhythm disturbance in detail. Individuals with CRD were included in the study. A series of long-term follow-up will be implemented to collect the volunteers’ health status and to ultimately generate a set of multiomics data. The characteristics of our research methods differ from those of research methods used in previous studies. Using multiomics analysis will help us not only explore the relationship between CRDs and the health of the molecules and signaling pathways in the body but also identify the molecular mechanisms by which CRDs affect physical health as well as detect potential clinical biomarkers and therapeutic targets. This research aims to establish an accurate health prediction model for individuals with CRD through multiple sets of scientific data and health assessments.

Our research design has three main characteristics: First, this is a prospective cohort study focusing on the health management of individuals with CRD. The various health assessment data and multiple sets of scientific data obtained in this study can be used as evidence to support the clinical application value of precision medicine. Second, this is a long-term cohort study. Data will be collected through multiple follow-up visits to assess the causal relationship and molecular mechanisms between circadian rhythm and sleep disorders, weakness, as well as illness. Third, this study will establish an accurate health prediction model based on multiomics analysis. Previous single-group studies have only revealed molecular data related to circadian rhythm disturbance at a single level. As this study will be using multiomics analysis, it can produce comprehensive and in-depth results.

This study will analyze the impact of CRDs on health status through health assessment and multiomics data to provide key evidence and an accurate prediction model for the health management of the CRD population. In addition, our data can serve as the basis for further routine health management and clinical disease research. At present, 100 volunteers who will be followed up for 5 years have been identified. However, we hope to increase the sample size and extend the follow-up period if our research resources would allow us to do so.

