### Study design and setting

This is a prospective, longitudinal cohort study. This study will begin in July 2022.Eligible volunteers with biological rhythm rules and biological rhythm disorders were recruited prospectively by key members of the research team who have been trained on inclusion/exclusion criteria and recruitment procedures. The participants will be visiting the hospital a total of 10 times for biological sample collection, lifestyle survey, and psychological evaluation every year. A general overview of the study is shown in Fig. 1.

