### Study population

Men and women aged between 18 and 40 years, with normal thinking and language expression ability, who have had a biological rhythm disorder for ≥3 months, and who could complete the physical examination as required and passed the physical examination were included in this study. Volunteers with any clinically diagnosed acute and chronic diseases, mental illness, or sleep disorders were excluded. Pregnant and lactating women were also excluded.

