### Measurements and instruments

#### General information

As general attributes, the volunteers’ sociodemographic characteristics, such as age, sex, education, occupation, marital status, history of disease, and duration of biological rhythm disorder, were and at follow-up will be documented. In addition, their average working hours per week, shift frequency, night shift schedule and frequency, day shift schedule and frequency, as well as work intensity were and at follow-up will be recorded.

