### Data analysis

Data on work, sleep, physical activity, fatigue, and concentration, among others, will be studied using horizontal cohort data analysis by group. Continuous variables with a normal distribution will be compared using *t* test or analysis of variance, whereas those with a non-normal distribution will be analyzed using a nonparametric test. Categorical variables will be analyzed using the *χ*^2^ test. The molecular expression of different horizontal queues will be compared using a computer.

Longitudinal cohort data analysis will be performed according to multipoint time order. Cluster analysis of longitudinal trajectories based on multiple sets of scientific data will be used. The machine learning method of binomial classification will be adopted to construct an accurate health prediction model for individuals with CRD based on multiomics data. Kolmogorov-Smirnov, F1, and receiver operating characteristic curves will be used to test the prediction sensitivity, specificity, and accuracy of the model.

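### The Discussion promises a causal assessment of circadian rhythm, but the between-group tests the article names are unadjusted and the cohort is not randomised

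*Protocol article*

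**What the plan says.** The causal wording is in the Discussion of the protocol article. Long-term follow-up is presented there as a way "to assess the causal relationship and molecular mechanisms between circadian rhythm and sleep disorders, weakness, as well as illness". Later the same section adds: "This study will analyze the impact of CRDs on health status through health assessment and multiomics data".

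The design is observational: "This is a prospective, longitudinal cohort study" (Study design and setting). Under Study population, eligibility covers people "who have had a biological rhythm disorder for ≥3 months", and the exclusion reads: "Volunteers with any clinically diagnosed acute and chronic diseases, mental illness, or sleep disorders were excluded".

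Under Data analysis, work, sleep, activity, fatigue and concentration data "will be studied using horizontal cohort data analysis by group". The tests listed are a t test or analysis of variance for normal data, a nonparametric test otherwise, and a chi-square test for categories. Molecular expression is also to be compared between groups, with no model named. The longitudinal methods are clustering of trajectories and a binary machine-learning classifier.

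Under General information, the study records age, sex, education and occupation, and also "average working hours per week, shift frequency, night shift schedule and frequency, day shift schedule and frequency, as well as work intensity", at baseline and at follow-up.

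**The concern.** Without randomisation, people with and without rhythm disruption, or with more and less of it, may differ in age, sex, education and working conditions. These can also relate to fatigue, mood, metabolic markers and omics profiles. A raw comparison of means or proportions mixes such differences with any effect of CRD. Clustering describes trajectories and a classifier predicts a label, so neither isolates an exposure effect either.

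Timing adds to the difficulty. CRD participants enter after at least three months of disruption, so the study has no measurement of them from before the disorder began. Sleep disorders and illness are outcomes in the causal sentence and also grounds for exclusion at entry.

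At stake is interpretation. If the analysis is carried out as written and read as the Discussion invites, unadjusted differences would be reported as effects of CRD.

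**Working it through.** The article gives no figure on this point to reproduce. It states 100 volunteers without a significance level, power, effect size, SD or group split. The check is therefore a reading of the text, followed by an illustration on assumed inputs.

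**Claim against method**

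| Needed for a causal reading | What the article provides |
|---|---|
| Control of confounding | No randomisation. No regression, matching, weighting, stratification or covariate set is named in Data analysis. |
| A model of exposure and outcome over time | Trajectory clustering (descriptive) and a binary classifier (predictive). |
| Measurement before exposure | CRD present for at least 3 months at entry. |
| A defined contrast | Study design and setting says "Eligible volunteers with biological rhythm rules and biological rhythm disorders were recruited prospectively". Baseline and follow-up visits describes all 100 recruits as having CRD. |

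The variables for a basic adjustment are on file under General information. Data analysis does bring in work data, but as something to be compared by group.

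**Illustration: what an unadjusted comparison can do**

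Assumptions, none from the documents:
- two groups of 50, outcome SD 1, two-sided 5% test, no true effect;
- one confounder that differs by d SD between groups and correlates r with the outcome within groups.

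Formulas:
- bias = d × r (in SD)
- SE = √(1/n₁ + 1/n₂) = √(1/50 + 1/50) = 0.20
- false-positive rate = P(Z > 1.96 − bias/SE) + P(Z < −1.96 − bias/SE)

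Results:
- d = 0.5, r = 0.3 (or d = 0.3, r = 0.5): bias 0.15 and bias/SE = 0.75. The rate is P(Z > 1.21) + P(Z < −2.71) = 0.117, about 12%.
- d = 0.5, r = 0.5: bias 0.25 and bias/SE = 1.25. The rate is P(Z > 0.71) + P(Z < −3.21) = 0.240, or 24%.
- Over d = 0.3 to 0.8 and r = 0.2 to 0.5, the bias runs from 0.06 to 0.40 SD and the rate from 6.0% to 51.6%.
- With a 70/30 split, SE = √(1/70 + 1/30) = 0.218 and the same range gives 5.9% to 45.0%.

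**Does adjustment help?**

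A simulation of 4,000 runs at 50 versus 50, with the confounder as a covariate, gave:

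| d, r | Unadjusted | Adjusted |
|---|---|---|
| 0.5, 0.3 | 10.6% | 5.1% |
| 0.8, 0.5 | 50.6% | 4.8% |

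Adjustment restores the nominal rate here because the only confounder is measured and modelled correctly. In the real study it can remove only confounding by measured variables.

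**The case against.** Four arguments count against making much of this.

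First, this is a journal article, and covariates are often left to a fuller protocol or analysis plan. The article does not say that the recorded variables will be ignored, and a reader who inferred so would go beyond the text. What stands is narrower: the article itself makes the causal statement and itself names the comparisons, and the two do not fit.

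Second, causation is not the primary aim. The Background gives that as a health promotion model, with exploratory objectives, and the Abstract speaks of outcomes associated with CRDs. Prediction and exploration do not require confounder adjustment. This is right, and it limits the weight of the point.

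Third, Specimen collection and processing takes samples from the same people around day and night shifts and after a 24-hour shift. Comparisons within a person hold sex, education and, within a visit, age and occupation fixed. Samples taken before a shift also precede that acute exposure, so it would be too sweeping to call all baseline omics post-exposure. However, Data analysis names no paired or within-person model.

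Fourth, it is tempting to conclude that the sample consists of people who tolerate disruption, so that harm will be hidden. The documents do not support that. Three months is a minimum duration, no data show who left exposure early, and excluding diagnosed disease is ordinary when new disease is an outcome. It also gives some time order for new diagnoses. Selection is possible, but its direction is unknown.

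**Conclusion.** The mismatch is real and worth correcting. The between-group tests named under Data analysis, applied to a non-randomised cohort whose CRD members are already exposed at entry, cannot support the causal statement in the Discussion. They can support association.

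How large the problem is in this study cannot be derived from the documents. The 12% to 24% figures show only what a bias of 0.15 to 0.25 SD would do in an assumed 50/50 contrast with no true effect. Reading 24% as this study's error rate would be wrong, since the split, the imbalance and the correlation are all assumed. If all 100 participants have CRD, there is no comparison with controls to bias. The contrast would then be between levels of exposure, where confounding remains possible but those figures do not apply directly.

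The point concerns one causal sentence and the methods attached to it. It does not reach the primary aim of building a health promotion model.

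**What to change.** In Data analysis:
- Make the main between-group and exposure-level comparisons regression models, with a mixed model for repeated measures, adjusted at least for age, sex and education.
- Put occupation, weekly hours and work intensity in a sensitivity model. They may track the shift exposure so closely that forcing them into the main model would remove the contrast of interest.
- Keep sleep, activity, diet and BMI out of the main model, because they may lie on the pathway from CRD to outcome.
- Analyse the samples taken around shifts as within-person contrasts.

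In the Discussion:
- Replace *causal relationship* by *longitudinal association*.
- State that CRD participants were already exposed, and free of diagnosed disease, when they entered.

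The cost is a few degrees of freedom and a softer claim. No new data are needed.

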### Trial status

Protocol version: v1.1, 01/01/2022.

The study began recruitment on 01/07/2022. We plan to complete recruitment by 31/12/2022.

## Data Availability

The dateset will available from ResMan, DOI: http://www.medresman.org.cn.

## Abbreviation

CRDs: Circadian rhythm disorders
